### Data collection

Patients will receive detailed written information on the aim of the study. After giving their written informed consent they will receive the questionnaire, containing the SF-36 [33], the PACIC 5A [35,36] and the PHQ-9 [42], and a stamped envelope with the postal address of the university. The patients are asked to return this questionnaire in the envelope to the university. Patients will also be informed that neither the GP nor the practice team has any possibility to get knowledge of their answers. The GP will create a list with the participants and allocate a code to each patient. This code is also marked on the questionnaires. The university only receives the patients' codes and has no access to their names. A second questionnaire is filled out by the GP and the practice nurse for each participant regarding current diagnostic findings (e.g. HbA1c, BD, LDL-cholesterol, weight, pulse etc.), comorbidities, medication, diabetes associated complications, compliance, smoking status and quality indicators for diabetes. This questionnaire is marked as well with the patient's code and will be returned to the university in a stamped envelope.

An independent research assistant of the university will enter the data directly into the SPSS program (version 18.0 or higher). Measurements and analysis will take place before randomization (pre-data-collection) and after 12 months (post-data-collection). Pre-data-collection is estimated to last 3 months (months 2 - 4).

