### Analysis

We aim to show the reduced level of HbA1c (primary endpoint) in the intervention group using a t-test for independent groups comparison. For binary outcome measures such as success meeting HbA1c, BP and LDL goals, logistic regression will be used to model the relationships between the outcome and treatment group, age and gender. Other potentially important covariates will be identified through exploratory analyses. The longitudinal aspect of the data can be incorporated into the model in various ways, we will utilize the model generalized estimating equations (GEE) approach [52].

For continuous outcomes such as HbA1c levels, blood pressure, lipid levels, SF-36 and the PACIC 5A a repeated measures analysis of variance is appropriate [53]. Fixed effect parameters will include treatment group, age, gender, and other potentially important covariates as the PHQ-9 score.

The primary data analysis will follow the intent-to-treat (ITT) approach where appropriate. This means that all available data from all individuals will be analyzed according to treatment group assignment, regardless of whether or not each individual actually received the assigned treatment.

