#### 2. Clinical intervention - Intervention on the patient

The Chronic Care Model has been shown to provide interactions between patients and providers that support optimal patient functional and clinical outcomes [57,58]. Practice nurses were chosen to implement and to deliver the intervention because of the ongoing need for assessment of goal attainment and because of their ability to work with patients to reduce ambivalence to behavior change, collaborate with GPs and reinforce diabetes education. In the European setting, external nurse practitioners do not exist or are not accepted by GPs. In contrast, the practice nurses are already integrated in the primary care setting and have a continuous relationship with study participants including both direct clinical interventions and collaboration with their GP.

The 6 key elements of the CCM will be addressed as follows:

Organization of health care: The specially trained practice nurse will be involved in care. She will monitor the patient during the study with the CARAT-tool. Contacts for monitoring are planned at least every 4 moths but the frequency can be increased according to the clinical situation of the patient. The clinical aim is to assure that standing orders for established clinical practice guidelines regarding frequency of laboratory testing (HbA1c, LDL, nephropathy screening), yearly ophthalmologic exam and performance of foot exam by the nurses facilitates are met.

Clinical information systems: The information on monitoring and appointments with the practice nurse will be collected in the CARAT-monitoring-tool and will be forwarded to the GP based on importance/urgency before the patient encounter to the GP. This way of information transfer between practice nurse and GP is new. This improvement in communication should help the GP to get an immediate overview on the current situation of the patient. It should also help to address current problems - as for instance a detected depression - more accurately. Data entry by the nurses into the registry allows the GP to obtain an overview on self-care goals, clinical parameters over time (BP, HbA1C, LDL, last ophthalmologic exam, aspirin use, foot exam) via a single sheet prior to each patient visit, and provides prompts for issues to be addressed at a given visit.

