For decision support, evidence-based information on diabetes care and patient information leaflets will be provided to the GPs during the interactive workshops. The practice nurses collaborate with the GP by sharing clinical and/or management issues and by providing guideline recommendations for diabetes [1] and depression [59], thus supporting the physician in appropriate decisions. Furthermore, a diabetes specialist of the department of endocrinology at the University Hospital of Zurich will be available for GPs to discuss urgent questions regarding the treatment, to facilitate referrals to specialized care and to make referrals more appropriate.

Self-management support, another key element of the CCM, will be addressed by the practice nurses in the follow-up appointments: Basic skills such as glucose monitoring, insulin administration, teaching about diabetes and its complications, and features of medical nutrition therapy are taught to the study participants with an emphasis on the patient's own life priorities and internal motivations. The aim is to assist the patient in selecting appropriate, concrete behavioral goals, in developing plans for reaching those goals and in evaluating the progress and adequacy of those plans. Specific behavior goals are based on ADA Clinical Guidelines [19] and include (a) dietary adherence, (b) moderate exercise 30 min for 3 days/week, adjusted for patient ability, (c) medication adherence and (d) monitoring.

To inform the patient about community resources, information leaflets will be provided by the practice nurses.

Individualized patient follow-up: Nurse case managers meet individually with patients in the treatment group throughout the study. On average, one hour is spent in each patient visit, with telephone and e-mail correspondence supplementing office visits where appropriate. Follow-up visits include reinforcement of behavior change goals, clinical assessments and attainment of clinical goals.

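### The covariate rule for the adjusted analyses is open to data-driven choice and does not limit PHQ-9 to its pre-randomisation value; the primary t-test is unaffected

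*Protocol article*

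**What the plan says.** The Analysis section of the protocol article describes three kinds of analysis.

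- **Primary.** HbA1c is compared between arms "using a t-test for independent groups comparison". No covariates are named for it.
- **Binary goals (HbA1c, blood pressure, LDL).** Logistic regression on treatment group, age and gender, with GEE for the longitudinal aspect. Beyond those terms: "Other potentially important covariates will be identified through exploratory analyses".
- **Continuous outcomes.** "For continuous outcomes such as HbA1c levels, blood pressure, lipid levels, SF-36 and the PACIC 5A a repeated measures analysis of variance is appropriate". For these models, "Fixed effect parameters will include treatment group, age, gender, and other potentially important covariates as the PHQ-9 score".

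No list of candidates, selection criterion or restriction to baseline variables is given, and nothing says that selection is made without sight of the treatment estimate. The PHQ-9 carries no time point.

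Other sections bear on the PHQ-9:

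- Table 1 and Confounder control present it as a measure of a potential confounder.
- Under Data collection, after consent, "they will receive the questionnaire, containing the SF-36 [33], the PACIC 5A [35,36] and the PHQ-9 [42"]. Measurements are taken before randomisation and after 12 months, and Timeframe of the study has the T1 measurement one year after T0.
- Under Clinical intervention, better information transfer should help the GP address current problems, "as for instance a detected depression - more accurately". Practice nurses also support decisions by "providing guideline recommendations for diabetes [1] and depression [59"].
- The Background says that depressed mood hampers self-management and can worsen glycaemic control.

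**The concern.** Two related weaknesses sit in two different models.

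**Selection.** The rule for the binary goals is a commitment to choose covariates from the trial data. Data collection supplies a wide pool: weight, pulse, comorbidities, medication, complications, compliance and smoking, with measurement planned at both waves. If the analyst can see the treatment estimate while choosing, the reported p-value no longer has its nominal meaning. The pool also contains post-randomisation values of things the intervention tries to change; medication adherence is one of its stated behavioural goals.

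**PHQ-9.** A confounder label is safe for a value taken before randomisation. A 12-month value can be a consequence of the intervention. Adjusting SF-36, PACIC 5A or HbA1c for it would estimate only the part of the effect that does not run through mood, which is not the effect the trial sets out to show.

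At stake are the claim that target attainment improves significantly, the quality-of-life and care-assessment results, and the reading of HbA1c if the t-test and the adjusted model disagree.

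**Working it through.** **1. The plan's own figure.** Inputs from Sample size: difference 0.5, SD 1.2, ICC 0.04, 12 patients per practice, power 80%, alpha 0.05 (taken as two-sided), drop-out 20%.

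- Patients per arm without clustering: 2 × (1.2 × (1.960 + 0.842) / 0.5)² = 90.4, so 91.
- Design effect: 1 + (12 − 1) × 0.04 = 1.44.
- Practices per arm: 91 × 1.44 / 12 = 10.92, so 11.
- With drop-out: 11 / 0.8 = 13.75, so 14 per arm and 28 in total.

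The stated size reproduces. It rests on an unadjusted comparison, so nothing in this point changes it.

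**2. Type I error under covariate selection.** The number of candidates and their strength are assumptions. Both set-ups use linear models with no true treatment effect; they stand in for the planned logistic/GEE models and do not reproduce them.

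*Patient level:* 168 / 1.44 ≈ 117 effective patients per arm, treated as independent, 3,000 runs per setting.

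| Candidates, correlation with outcome | Selected by association with outcome | Set with smallest treatment p-value |
|---|---|---|
| 3, 0.2 | 5.1% | 8.7% |
| 5, 0.2 | 5.0% | 12.4% |
| 5, 0.3 | 5.4% | 17.8% |

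*Practice level:* 28 practice means, candidate coefficients 0.25, up to two covariates kept.

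- Keeping the two covariates most associated with the outcome gives just under 5% with 4 or with 8 candidates.
- Keeping the set with the smallest treatment p-value gives 10% to 11% with 4 candidates and 16% to 18% with 8, across repeated runs.

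The inflation comes entirely from letting the treatment result steer the choice.

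**3. PHQ-9 as a mediator, HbA1c.** The mediated share is an assumption. Remaining effect = 0.5 × (1 − share). Power = Φ(effect / SE − 1.96), with SE = 1.2 × √(2 / n_eff). For 14 × 12 per arm, n_eff = 168 / 1.44 = 116.7 and SE = 0.157. For 11 × 12, n_eff = 132 / 1.44 = 91.7 and SE = 0.177.

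| Share through mood | Effect left | Power, 14 × 12 | Power, 11 × 12 |
|---|---|---|---|
| 0% (or baseline PHQ-9) | 0.50 | 88.9% | 80.5% |
| 10% | 0.45 | 81.7% | 71.9% |
| 20% | 0.40 | 72.1% | 61.7% |
| 30% | 0.35 | 60.6% | 50.6% |
| 50% | 0.25 | 35.6% | 29.1% |

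The SD is held at 1.2. Adjustment would also reduce residual variance somewhat, so the power figures are illustrative; the lost effect is the main point.

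To see what shares are conceivable: amount removed = PHQ-9 shift × HbA1c slope per PHQ-9 point. An assumed shift of 1 to 2 points and slope of 0.02 to 0.10 remove 0.02 to 0.20 HbA1c points, which is 4% to 40% of 0.5. The documents give neither value.

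**4. PHQ-9 as a mediator, SF-36.** If the intervention improved PHQ-9 by 0.2 SD and PHQ-9 correlated −0.6 with an SF-36 mental score (both assumed), adjusting for the 12-month value would remove 0.2 × 0.6 = 0.12 SD of real benefit. Halving either assumption halves this to 0.06 SD.

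**The case against.** A reader might infer three stronger things, and the documents support none of them.

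- *That the primary result is compromised.* The primary t-test has no covariates. Only the binary goals, the other continuous outcomes and the supplementary adjusted HbA1c model are exposed.
- *That the plan inflates type I error.* It allows inflation but does not prescribe it. Nothing in the Analysis section describes picking covariates by the treatment p-value, and selection by association with the outcome holds the error at about 5%. The selection sentence also belongs to the logistic/GEE paragraph; the PHQ-9 is named in advance, with a rationale, for a different set of models.
- *That the plan adjusts for 12-month PHQ-9.* It does not say so. A repeat PHQ-9 is implied by the schedule but not named, and the confounder label fits a baseline value, which would be harmless.

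Two further objections have weight. Which visit supplies a covariate is often settled in the analysis plan, which is not shown. And depression is a modest part of the intervention: it appears as an example and in guideline material, it is absent from the listed course content and monitoring-tool items, and practices cannot see patients' PHQ-9 answers. A large effect on mood is therefore not something the documents establish.

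What remains is that the selection sentence is a stated rule, not a silence. An analysis plan with a fixed list would depart from it, and one that follows it inherits the weakness. The PHQ-9 sentence, placed in a repeated-measures model where a 12-month value could enter, needs the same short repair.

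**Conclusion.** The point holds as a weakness in the adjusted and secondary analyses. Covariates for the binary-goal models may be chosen from trial data without a stated safeguard, and the PHQ-9 in the continuous-outcome models is not confined to baseline.

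The size is conditional. Type I error could reach about 9% to 18% with 3 to 8 candidates if selection responds to the treatment estimate; it stays near 5% otherwise. Adjusting for a 12-month PHQ-9 would leave 0.45 to 0.35 of the 0.5-point HbA1c effect if 10% to 30% of it ran through mood, and could similarly shrink SF-36 and PACIC 5A differences. The candidate numbers, correlations and mediated shares are assumptions, not figures from the protocol. The primary test and the 28 practices stand as planned. This is a cheap improvement worth making before the data are analysed.

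**What to change.** Replace the exploratory-selection sentence with a fixed, baseline-only covariate set for each adjusted model: the T0 value of the outcome, age, gender, and T0 PHQ-9 where adjustment for depression is wanted. State that no post-randomisation PHQ-9, and no other post-randomisation variable, enters an effectiveness model. Label any model with covariates found by exploration as a sensitivity analysis. If the 12-month PHQ-9 is of interest, analyse it as an outcome.

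No terms for randomisation factors are needed, because Recruitment of GPs and randomization imposes no constraint on the allocation.

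The cost is a few sentences of analysis text. No new data are needed and the sample size does not change. The team gives up one option: covariates added later count only as sensitivity analyses.

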### Primary outcome

The primary outcome is the glycated haemoglobin (HbA1c) level. The power calculation is based on this parameter.

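### The primary endpoint HbA1c is placed under a t-test and again, unranked, under a repeated-measures ANOVA, and neither names the baseline HbA1c already collected as a covariate

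*Protocol article*

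**What the plan says.** All references are to the protocol article.

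- **Primary outcome:** "The primary outcome is the glycated haemoglobin (HbA1c) level". The section does not say whether this means the value at 12 months or the change from baseline.
- **Analysis, opening sentence:** "We aim to show the reduced level of HbA1c (primary endpoint) in the intervention group using a t-test for independent groups comparison". No covariate is mentioned.
- **Analysis, next paragraph:** "For continuous outcomes such as HbA1c levels, blood pressure, lipid levels, SF-36 and the PACIC 5A a repeated measures analysis of variance is appropriate". The section then adds: "Fixed effect parameters will include treatment group, age, gender, and other potentially important covariates as the PHQ-9 score". Time, group-by-time and baseline HbA1c are not among the listed terms, and the list is open.
- **Data collection:** "Measurements and analysis will take place before randomization (pre-data-collection) and after 12 months (post-data-collection". HbA1c is one of the findings recorded on the practice questionnaire, so each patient should have a value from before allocation.
- **Sample size:** mean 7.7% at baseline, difference 0.5 points, SD 1.2, ICC 0.04, 80% power, 5% significance, 12 patients in each of 11 practices per arm, raised to 14 practices for 20% drop-out. No baseline/follow-up correlation appears.

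**The concern.** There are two linked weaknesses.

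**Room for choice.** HbA1c appears under two methods, and the text does not say what the second is for. The t-test could be run on the 12-month value or on the change. The ANOVA could be read through its group term or through a group-by-time term, with covariates still to be settled. These versions can give different answers for the result that decides the trial. If the choice is not fixed beforehand, nobody can later show that it was made independently of the data.

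**Unused baseline.** HbA1c before treatment is usually informative about HbA1c a year later. Leaving it out as a covariate gives up precision. If the t-test uses follow-up values only, it also leaves in place any chance difference between arms at the start. Only 28 practices are randomised, and the randomisation section says that no constraint is imposed, so some chance difference is to be expected.

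**Working it through.** **Step 1: reproduce the plan's figure.** Inputs are from the Sample size section. Two-sided 5% is assumed; the section does not state sidedness, but one-sided testing gives 8.64, i.e. 9 practices, and does not match.

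- Patients per arm without clustering: 2 × [1.2 × (1.960 + 0.842) / 0.5]² = 90.4, so 91.
- Design effect: 1 + (12 − 1) × 0.04 = 1.44.
- 91 × 1.44 = 131.0 patients; 131.0 / 12 = 10.92, so 11 practices per arm.
- 11 / 0.8 = 13.75, so 14 per arm and 28 in total.

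The stated numbers reproduce. They correspond to a comparison of HbA1c level that allows for clustering and does not adjust for baseline.

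**Step 2: power at 11 practices per arm.** Effective n per arm = 132 / 1.44 = 91.67. Unadjusted SE = 1.2 × √(2 / 91.67) = 0.177, and 0.5 / 0.177 = 2.82. With baseline HbA1c as covariate, the SD becomes 1.2 × √(1 − r²). With a change score, or equivalently the group-by-time test at two time points, it becomes 1.2 × √(2(1 − r)). Here r is the baseline/follow-up correlation. It is an assumption (range 0.3 to 0.7), and the same ICC is used throughout.

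| Analysis | r | Normal approx. | t, 20 df |
|---|---|---|---|
| 12-month value, unadjusted | any | 80.5% | 76.5% |
| Baseline as covariate | 0.3 | 84.1% | 80.3% |
| Baseline as covariate | 0.5 | 90.3% | 87.2% |
| Baseline as covariate | 0.7 | 97.7% | 96.4% |
| Change / group-by-time | 0.3 | 66.4% | 62.1% |
| Change / group-by-time | 0.5 | 80.5% | 76.5% |
| Change / group-by-time | 0.7 | 95.4% | 93.3% |

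The two right-hand columns should not be mixed. The fall from 80.5% to 76.5% comes from using a t reference with 2 × (11 − 1) = 20 df, not from omitting baseline. Spending one df on the covariate (19 df) lowers the adjusted t figures by about 0.2 points or less.

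The group main effect of a two-time-point ANOVA would do much worse. It averages a null baseline difference with the follow-up difference, so the effect is 0.25 with SD 1.2 × √((1 + r)/2). Power is 41.7%, 37.0% and 33.4% at r = 0.3, 0.5 and 0.7 (normal approximation). The section does not say which term would be read.

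**Step 3: what choosing between analyses could do.** Suppose each test is correctly sized on its own. The follow-up-only statistic and the change statistic then have correlation √((1 − r)/2), which is 0.59, 0.50 and 0.39 at r = 0.3, 0.5 and 0.7. By simulation, claiming success when either is significant at 5% gives a type I error of 8.8%, 9.1% and 9.4%. Under the planned effect the two disagree on significance in 26%, 22% and 20% of trials.

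**Step 4: chance baseline difference.** With all 14 practices (168 patients) per arm, SE = √(2 × SD² × 1.44 / 168), applying the planned ICC to baseline. The planned SD of 1.2 may be too large here: inclusion requires HbA1c above 7.0% and the assumed mean is 7.7%, so baseline is truncated close to its mean. A range is therefore shown.

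| Assumed baseline SD | SE | P(difference ≥ 0.2 either way) |
|---|---|---|
| 0.7 | 0.092 | 3% |
| 0.9 | 0.118 | 9% |
| 1.2 | 0.157 | 20% |

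**The case against.** The best defence is that the plan does identify its primary analysis. Only the t-test is attached to the primary endpoint, the sample size matches a simple two-group comparison of level, and the repeated-measures sentence is a general one covering several continuous outcomes. That reading is the more natural one. A reader might infer that nothing at all indicates which test decides the trial; the text does not support going that far. What remains is that HbA1c is named first in the second list with no word on its role there, and that the t-test's own input (value or change) is not given.

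A second defence is that baseline is not ignored. With two time points, a group-by-time test is a change-score test and subtracts the baseline difference, as would a t-test on change. This stands. It would be wrong to say that baseline imbalance goes uncorrected under every reading; that is true of a follow-up-only t-test, for example. Baseline HbA1c is also unnamed rather than excluded, since the covariate list is open.

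Third, an unadjusted comparison of randomised arms is unbiased, so omitting a covariate is a loss of efficiency and not an error, and a condensed article may leave modelling detail to a fuller document. The efficiency part is accepted. The article is not merely silent, however: it states two methods for one primary endpoint and does not rank them.

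Finally, the gain depends on r, which the documents do not give. At r = 0.3 it is under 4 points, and inclusion only above 7.0% may lower r.

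**Conclusion.** The point holds as one of incomplete specification and avoidable inefficiency. The t-test is probably primary, but its form is unstated, and an unranked second model with open covariates leaves room for choice. Baseline HbA1c is a named covariate in neither.

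Adjusting for it would add about 4, 10 or 17 points of power at assumed correlations of 0.3, 0.5 and 0.7 (normal approximation), or about 4, 11 or 20 points on 20 df. It would also deal with a chance baseline difference that a follow-up-only t-test leaves in place. The chance of a difference of at least 0.2 points, against a target effect of 0.5, is 3% to 20% for an assumed baseline SD of 0.7 to 1.2.

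Two stronger readings are tempting and not supported. One is that the trial is underpowered because baseline is left out: the stated sample size reproduces and gives about 80% power on its own normal-approximation terms. The other is that the type I error is in fact 8.8% to 9.4%: that would follow only if the better of two tests were taken, which the protocol does not say will happen.

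Whether the HbA1c analyses allow for clustering by practice is a separate question and carries no weight here.

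**What to change.** Name one primary analysis in the Analysis section: a linear mixed model of 12-month HbA1c on arm, with baseline HbA1c as a prespecified covariate and practice as a random effect, reporting the adjusted mean difference with its 95% CI. State in the Primary outcome section that the endpoint is the 12-month value. If other covariates are wanted in this model, list them in advance.

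Label any t-test of HbA1c as a sensitivity analysis at practice level. Either remove HbA1c from the repeated-measures list or mark that analysis as supportive, with the term that carries the treatment effect named.

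The data are already planned for, and the sample size need not change. The cost is a few sentences and one degree of freedom, provided the choice is fixed before outcome data are compared between arms.
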